## Behaviour Change Communication (BCC) Intervention

All study arms will receive behaviour change communication (BCC) provided by CHW during their monthly household visits. The mHealth intervention arms will receive the additional mHealth BCC that will consist of audio messages transmitted to the recipient’s mobile phone. Provision of BCC messaging will be randomized among the groups at cluster (camp) level. The planned development strategy for the mHealth BCC messages has the following key points:

- - Messaging will be developed in collaboration with Shaqodoon and Media Inc., which are companies based in Somalia and are specialists in interactive voice response (IVR) technology and creative message development, respectively.
  - Currently, we plan to deliver 12 audio messages, with two messages focused on each of the 6 health and nutrition topics listed in Table 1 below. These topics were identified as major barriers to optimal nutrition in the REFANI research.
  - Messaging will be designed following a human centred design approach, will be culturally appropriate, and will be produced using local voice actors and musicians.
  - Message content will be tested to ensure it is compelling and effective. Different formats for message delivery will be tested, such as a 6-12 episode soap opera series, or standalone short/succinct messages.
  - The messages produced will be piloted with small groups of IDP living in the same area as the study population, and revised during several iterative rounds of development prior to general use.
  - Full consideration will be given to ensuring the messaging will be acceptable to all parties of the conflict. This will ensure that listening to the message does not put any beneficiaries at risk.

Table 1 List of Topics to be Covered in mHealth Messaging

[figure not shown]

The developed audio messages will be delivered via a server, connected to the cellular network, to the registered mobile phone/SIM card of the participants in the BBC arm of the study. Figure 3 illustrates the messaging flow and associated data capture. Cash transfers are not conditional on listening to the audio messages but information on the number of messages listened to and the duration of the listening will be recorded.

Figure 2 Flow Diagram of Audio Messaging for Participants in the BCC Arm

[figure not shown]

During their monthly household visits, CHW will support defaulter tracing, awareness raising, and community engagement in addition to the standard health and nutrition messaging work that is done routinely during household visits. These routine activities will be done equally in all study camps. To remove any potential bias between study arms due to differences in the quality of CHW services, CHW volunteers may be rotated between the camps in the different study arms. CHWs are volunteers but will be paid a monthly incentive

# Study Design

The research will take place in 20 IDP camps in the Afgooye Corridor, which are expected to contain an average population size of 65 children (aged 0-59 mo.) per camp. A 2x2 factorial design will be used with cluster randomization. A cluster will comprise one IDP camp. The study design is illustrated below.

Table 2 Study Design Summary

|  | Unconditional  Cash Transfer | Conditional  Cash Transfer |
| --- | --- | --- |
| No mHealth BCC | 5 camps | 5 camps |
| mHealth BCC | 5 camps | 5 camps |

All households within the 20 selected IDP camps will be invited to participate in the study so it is anticipated that a total of 1,300 children will be recruited. Measurements will be taken at monthly household visits, which will be done by community health workers, and continue during the course of the intervention. Children who exceed the age of 59 mo. during the course of the study will continue to be followed until the end of the follow-up period. Any new households that arrive in the IDP camps after the household recruitment has finished will not be invited to enrol.

Participant exclusion criteria:

1. Children with a disability that prevents taking weight or height measures

2. Children with a medical condition that prevents them eating a normal diet

3. Children confined to bed due to illness

4. Children living in a household in which the mother/carer is unable to respond to questions due to a speech or hearing impairment

This study design will allow us to address 2 main hypotheses:

(1) Humanitarian cash transfer conditionality improves health service utilization, increases vaccination coverage by 20%, and reduces morbidity in children aged 6-59 months.

This hypothesis will be tested by comparing the 10 clusters receiving unconditional cash with the 10 clusters receiving conditional cash transfers.

(2) A mHealth mobile phone BCC messaging intervention, linked to cash transfers, will improve health knowledge and nutrition related behaviours in a complex emergency context.

This hypothesis will be tested by comparing the 10 clusters who receive the mHealth intervention with those that do not. We will also test the secondary hypothesis that a combined conditional cash transfers and mHealth mobile phone BCC messaging intervention reduces the risk of acute malnutrition compared to those receiving unconditional cash transfers or no mHealth intervention.

# Outcome measures

- Measles vaccination coverage - % of children 9-<59 months of age who received measles vaccine
- EPI vaccination coverage - % of children 0-<59 months of age who received all vaccines required by the national vaccination protocols
- Child diet diversity score of children 6-<24 months of age
- Parental/caretakers knowledge of BCC health and nutrition topics

The secondary outcomes of interest are:

- Incidence of acute malnutrition - MUAC<12.5 cm or oedema among children 6-59 months
- Incidence of mortality among children 6-59 months
- Exclusive breastfeeding prevalence - % of infants 0-5 months who were exclusively breastfed during the last 24 hours ​
- Incidence of child morbidity
- Causes of death ascertained by Verbal Autopsy

# Sample Size Calculations

The sample size available to test for differences in vaccination coverage (hypothesis 1) was assessed using clustersampsi in Stata v14. Based on current measles vaccination coverage data, collected during the REFANI trial, we expect to see a baseline coverage of around 64%. With 10 clusters (camps) per arm and an average population of 65 children (aged 0-59 months) per cluster, and allowing for an alpha risk of 0.05, a power of 0.8, and an ICC of 0.06, we will be able to detect a minimum increase of 18 percentage points. This minimum detectable difference lies below our hypothesized effect size of 20 percentage points.

To calculate a sample size to test hypothesis 2 - the effect of mHealth messaging on health knowledge and nutrition behaviours - we assumed that there will be no interaction between the mHealth and conditionality interventions. Under this assumption we assessed the utility of the available sample size to detect a difference in children’s diet diversity score between the clusters receiving the mHealth intervention and those that won’t. Based on data from the REFANI study we expect to see a baseline child diet diversity score of 3 and a SD of 2. With 10 clusters (camps) per arm and an average population of 65 children (aged 0-59 months) per cluster, and allowing for an alpha risk of 0.05, a power of 0.8, and an ICC of 0.01, we will be able to detect a minimum increase of 0.42 in the diet diversity score. These calculations confirm that the study design is well powered to detect differences in our primary outcomes.

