| Unnoticed and forceful eviction of research participants from IDP camps | Proper follow up and defaulter tracing mechanism will be employed to ensure that as many as possible participants complete the entire study duration. |
| Discontinuation of cash transfers which causes participants to seek humanitarian assistance in other areas. | Concern will work with donors, MOH and partners to conduct the study in areas most in need of CTP over the program period. |

During the previous REFANI-S study, Concern and UCL have developed robust approaches to ensure the quality of quantitative and qualitative data collection in a difficult security context where international researchers are generally not allowed full access and where many local staff have not had the opportunity to pursue advanced training. The HR strategy has been to recruit strong Somali nationals and invest heavily in their training and support, including UCL by researchers that provide regular training, mentoring and close supervision.

The Study Coordinator is from Kenya and is able to visit the study sites regularly and provide technical support to the teams.

In addition, the team on the ground are supported by the Concern Somalia Health and Nutrition Coordinator, Dublin based health, nutrition and research advisors, as well as the Somalia Programme Director, who has experience in research and program management. This approach has allowed Concern and UCL to build up a strong cadre of Somali research staff for quantitative and qualitative data collection. This team will be utilized during the CINS research and the same approach used, thereby building local capacity and ensuring a deep understanding of the local context.

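### The detectable diet-diversity difference of 0.42 carries no stated allowance for non-participation, loss or unequal camp sizes, so the stated 80% power has no margin

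*Protocol*

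**What the plan says.** The second paragraph of Protocol, Sample Size Calculations, treats hypothesis 2 as a comparison of mean diet diversity scores. Its inputs are "With 10 clusters (camps) per arm and an average population of 65 children (aged 0-59 months) per cluster", "an alpha risk of 0.05, a power of 0.8, and an ICC of 0.01", and, from the earlier REFANI study, "we expect to see a baseline child diet diversity score of 3 and a SD of 2". It concludes: "an ICC of 0.01, we will be able to detect a minimum increase of 0.42 in the diet diversity score". The section ends by saying that these calculations confirm adequate power for the primary outcomes. It states no loss rate, participation rate or camp-size CV.

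Other sections bear on how many children will be analysed:

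- **Study Design** gives 65 as the average number of children living in a camp, and puts the number of children to be recruited thus: "All households within the 20 selected IDP camps will be invited to participate in the study so it is anticipated that a total of 1,300". It lists four exclusion criteria, and adds: "Any new households that arrive in the IDP camps after the household recruitment has finished will not be invited to enrol".
- **Ethical Review** requires caregiver consent and grants a right to withdraw.
- **Cash Transfer Intervention** plans nine months of transfers, and Study Design has measurement continuing throughout the intervention.
- **Risk Management, Table 3** lists "Unnoticed and forceful eviction of research participants from IDP camps" and "Discontinuation of cash transfers which causes participants to seek humanitarian assistance in other areas".
- **Outcome measures** defines the diet diversity score only for children aged 6-<24 months.

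**The concern.** One number, 65, stands for three different quantities: children resident in a camp, children recruited (20 x 65 = 1,300, exactly the anticipated total) and children analysed. The protocol's own provisions separate the three. Exclusion and refusal come between resident and recruited; withdrawal, eviction and departure come between recruited and analysed. Households that leave are not replaced by new arrivals.

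Camp size is a second matter. A cluster is a whole camp with every household invited, so nothing in the design equalises cluster sizes, and 65 is only a mean. The design effect that reproduces 0.42 is the one for equal clusters.

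What is at stake is how the mHealth comparison will be read. If the true power for 0.42 is below the stated 80%, a null result on the diet score will be given somewhat more weight against an effect than it deserves.

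**Working it through.** **Inputs from Sample Size Calculations.** k = 10 camps per level of the mHealth factor, m = 65 children per camp, SD = 2, ICC = 0.01, alpha = 0.05 (taken as two-sided, which reproduces the figure), power 0.80.

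**Assumptions, not in the documents.** Combined non-participation and loss of 10-20%, applied evenly across camps; camp-size CV of 0.5.

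**Formulas.**

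- Design effect: DE = 1 + [(1 + CV²)m − 1] x ICC
- Standard error of the difference: SE = SD x √(2 x DE / (k x m))
- Minimum detectable difference: MDD = (t₀.₉₇₅ + t₀.₈₀) x SE on 2(k − 1) = 18 df, that is (2.101 + 0.862) x SE = 2.963 x SE
- Power at 0.42 from the noncentral t with 18 df

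**Reproducing the protocol's figure.** With m = 65, CV = 0 and no loss:

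- DE = 1 + 64 x 0.01 = 1.64
- SE = 2 x √(2 x 1.64 / 650) = 0.1421
- MDD = 2.963 x 0.1421 = 0.421
- Power at 0.42 = 79.8%

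The stated 0.42 is therefore the no-allowance value.

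**Adding loss and unequal size.**

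| Assumption | m | DE | SE | MDD | Power at 0.42 |
|---|---|---|---|---|---|
| None (as stated) | 65 | 1.640 | 0.1421 | 0.421 | 80% |
| 10% loss | 58.5 | 1.575 | 0.1468 | 0.435 | 77% |
| 20% loss | 52 | 1.510 | 0.1524 | 0.452 | 74% |
| CV 0.5, no loss | 65 | 1.803 | 0.1489 | 0.441 | 76% |
| CV 0.5 and 20% loss | 52 | 1.640 | 0.1588 | 0.471 | 71% |

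The unequal-size design effect is slightly pessimistic if the analysis weights camps optimally. Simulation with gamma-distributed camp sizes puts the last row at about 72% rather than 71%.

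**The age band, for scale.** If ages were spread evenly over 0-59 months (an assumption), 18/60 x 65 = 19.5 children per camp would fall in 6-<24 months. Then DE = 1.185, SE = 0.2205 and MDD = 0.653, with about 44% power at 0.42. Adding CV 0.5 moves the MDD to 0.667. With CV 0.5 and 20% loss (m = 15.6), power at 0.42 is about 36%.

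**The measles figure.** The stated inputs are 64% baseline, ICC 0.06 and the same camps. With no allowance, DE = 1 + 64 x 0.06 = 4.84. At 80% coverage, SE = √[(0.64 x 0.36 + 0.80 x 0.20) x 4.84 / 650] = 0.0539, and 2.963 x 0.0539 = 0.160. The detectable increase is thus 16.0 points, against the stated 18. At 20% loss it is 16.3 points, and with CV 0.5 added 17.6.

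**The case against.** The protocol does not say which test lies behind 0.42, so a hidden allowance cannot be excluded. Under a two-sided normal approximation the no-allowance value is 0.398, while 15% loss (0.419), CV 0.5 (0.417) or 10% loss with CV 0.3 (0.418) would each round to 0.42. A reader might infer that 0.42 can arise only from exactly 65 analysed children in every camp; the text does not establish that. What remains is that no allowance is stated, and that the t calculation, the appropriate one with 18 df, gives 0.42 without any.

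A reader might also infer that the plan expects evictions and departures. It does not say so. Table 3 lists them as risks answered by follow-up, defaulter tracing and work with donors, and Risk Management assumes that security will not deteriorate. Differing camp size is likewise an inference from the word average and from whole-camp enrolment.

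The effect is moderate. The MDD rises by 0.01-0.03 for 10-20% loss, on a score with SD 2, and the protocol sets no target effect for the diet score, so no target is missed. Covariate adjustment and repeated data collection, both planned, could recover some precision, though the amount is unknown. To say that 80% power fails under any realistic retention would go too far, since the documents give no retention figure.

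Finally, a reader might extend the point to hypothesis 1. That fails: the stated 18 points already exceeds the 16.0 that its inputs give, and covers 20% loss with CV 0.5 (17.6). Even CV 0.7 with 20% loss gives 18.8, below the hypothesised 20.

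**Conclusion.** The point holds for the diet diversity score only, as an unstated planning allowance and not as an arithmetic error: 0.42 follows from its inputs. Because those inputs give 79.8% power at 0.42 on the t calculation, any exclusion, refusal, loss or variation in camp size puts power below the stated 80%. That direction does not depend on the assumed rates. The size does: it ranges from 0.435 (77% power at 0.42) at 10% loss to 0.471 (71%) with 20% loss and CV 0.5.

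These figures use m = 65 and would be superseded once the calculation is restricted to the outcome's age band, which matters more. The allowances would still be needed after that restriction, and the losses compound. It is worth correcting, at moderate importance.

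**What to change.** In Sample Size Calculations, recompute the diet-score MDD as follows:

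1. Replace 65 by the expected number of analysed children aged 6-<24 months per camp: residents in that band, times the proportions eligible, consenting and retained. State each rate and its source; the earlier REFANI study in the same corridor is the natural one.
2. Use DE = 1 + [(1 + CV²)m − 1] x ICC, with the CV taken from the household listing that the cash distribution team makes in each camp.
3. State the test, its degrees of freedom and its sidedness, so that the figure can be reproduced.
4. Restate the MDD and limit the section's closing claim of adequate power to what it supports for this outcome.

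The cost is a recalculation and a few sentences. No extra camps are needed, and the measles figure can stand on this ground. The only downside is a less favourable stated figure.

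### The hypothesis 2 power figure for diet diversity counts every under-five in the camp, although the outcome covers only children aged 6 to under 24 months

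*Protocol*

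**What the plan says.** The Outcome measures section of the Protocol opens with an unheaded list of four outcomes, followed by the secondary outcomes. One of the four is "Child diet diversity score of children 6-<24 months of age".

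The Sample Size Calculations section uses this score, and no other outcome, to assess hypothesis 2. Its inputs are:

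- Cluster number and size: "With 10 clusters (camps) per arm and an average population of 65 children (aged 0-59 months) per cluster".
- Mean and spread: "we expect to see a baseline child diet diversity score of 3 and a SD of 2".
- Error rates and clustering: "allowing for an alpha risk of 0.05, a power of 0.8, and an ICC of 0.01".

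The result is "we will be able to detect a minimum increase of 0.42 in the diet diversity score". The section closes: "These calculations confirm that the study design is well powered to detect differences in our primary outcomes".

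The Study Design section shows what the 65 stands for. Camps are "expected to contain an average population size of 65 children (aged 0-59 mo.) per camp", and across the 20 camps "it is anticipated that a total of 1,300 children will be recruited", which is 20 x 65. The 65 is therefore the whole under-five population of a camp.

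**The concern.** The calculation and the outcome definition cover different children. A child aged 3 years is counted in the 65 but has no place in an outcome limited to 6 to under 24 months. Nowhere does the Protocol narrow the 65 to the eligible ages, give the number of children in that age band, or define the diet diversity outcome for all under-fives.

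This matters because hypothesis 2 is one of the trial's two main hypotheses and diet diversity is the only outcome sized for it. Anyone who relies on the Protocol to judge what the mHealth comparison can show will take 0.42 at 80% power as the trial's sensitivity.

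**Working it through.** **Inputs from the Protocol.** k = 10 camps per arm (the factorial margin, 10 against 10), SD = 2, ICC = 0.01, alpha = 0.05, power = 0.80, and m = 65 children per camp as entered. Sidedness is not stated; two-sided is the reading that reproduces the figure.

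**Formulas.**

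- Design effect: DE = 1 + (m - 1) x ICC
- Standard error of the difference: SE = SD x sqrt(2 x DE / (k x m))
- Detectable difference: MDD = (t[0.975; 18 df] + t[0.80; 18 df]) x SE, with 18 = 2 x (10 - 1). The two quantiles are 2.101 and 0.862, which sum to 2.963.
- Power at 0.42: noncentral t with 18 df and noncentrality 0.42 / SE

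**Step 1: reproduce the stated figure (m = 65).**

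- DE = 1 + 64 x 0.01 = 1.64
- SE = 2 x sqrt(2 x 1.64 / 650) = 0.142
- MDD = 2.963 x 0.142 = 0.421, matching the stated 0.42
- Power at 0.42 = 79.8%

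Other variants at m = 65 do not match: two-sided normal gives 0.398, one-sided t 0.369 and one-sided normal 0.353. Solving the t formula for the cluster size that yields 0.42 gives m of about 65.5. The figure was therefore computed on all under-fives.

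**Step 2: repeat with eligible children only.** The Protocol gives no age distribution. Assume ages are spread evenly over the 60 months of the 0-59 band. The 6 to under 24 month band covers 18 of them, so m = 65 x 18/60 = 19.5 per camp, or 195 per arm.

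- DE = 1 + 18.5 x 0.01 = 1.185
- SE = 2 x sqrt(2 x 1.185 / 195) = 0.220
- MDD = 2.963 x 0.220 = 0.65 (0.62 by normal approximation)
- Power at 0.42 = 44% (48% by normal approximation)

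**Step 3: vary the assumption.**

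| Eligible children per camp | Share of 65 | DE | MDD | Power at 0.42 |
| --- | --- | --- | --- | --- |
| 13 | 20% | 1.12 | 0.78 | 33% |
| 16 | 25% | 1.15 | 0.71 | 38% |
| 19.5 | 30% | 1.185 | 0.65 | 44% |
| 26 | 40% | 1.25 | 0.58 | 53% |
| 30 | 46% | 1.29 | 0.55 | 57% |
| 65 (as entered) | 100% | 1.64 | 0.42 | 80% |

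The design effect falls as clusters shrink, so the loss is less than proportional. Even so, at 19.5 per camp the MDD is about 55% larger (0.653 / 0.421 = 1.55).

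**The case against.** **The 0.42 is correct for its inputs.** This stands. The section openly declares the 0-59 month age range it uses. The fault is an inconsistency between two sections, not a slip of arithmetic.

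**The 0.65 is not in the documents.** This also stands. It rests on an assumed age spread and carries over an SD of 2 from the earlier REFANI study, whose age range for that SD the Protocol does not state. It should be given as a range. No row in the table above, however, brings back 0.42 at 80% power.

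**All under-fives may be intended.** The Quantitative Data collection section puts the 24-hour dietary recall on the questionnaire for children aged 0-59 months, and the sample size text names the score without an age limit. But collecting data more widely does not redefine the outcome. If all ages are meant, the outcome definition has to change, so the two sections still need reconciling.

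**Repeated visits and covariate adjustment could recover precision.** They could, and children will age into and out of the band during follow-up. The stated calculation claims none of this. It also makes no allowance for dropout or unequal camp sizes, which would raise the detectable difference.

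**Stronger readings that the documents do not support.**

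- A reader might infer that power at 0.42 is far below one half. The central value is 44%, and it passes 50% if about 40% of under-fives are eligible.
- A reader might apply the vaccination ICC of 0.06 to diet diversity and obtain 0.87. The Protocol assigns 0.01 to this outcome and gives no ground for borrowing the other value.
- A reader might infer that the well-powered claim is false, or that a null result will be taken to exclude 0.42. The Protocol states no target effect for diet diversity and does not say how a null result would be read. Hypothesis 2 also covers health knowledge, so diet diversity alone would not decide it.
- A reader might fault the lack of separate calculations for full EPI coverage and caregiver knowledge. Not sizing every outcome is common practice; only the breadth of the closing sentence is open to criticism.

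**Conclusion.** The point holds as a wrong stated figure. The 0.42 at 80% power describes a comparison of all under-fives, not the outcome the Protocol defines. Keeping the Protocol's SD, ICC, alpha and number of camps, the detectable difference for the defined outcome is about 0.65 under an even age spread, and 0.78 to 0.55 for 13 to 30 eligible children per camp. Power at 0.42 is about 44%, with a range of about 33% to 57%.

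The direction is not in doubt, because any real restriction of the 65 raises the detectable difference. The exact size depends on an age distribution the Protocol does not give. For diet diversity, the well-powered statement is unsupported rather than shown to be false: it rests on the 0.42, and there is no stated effect to compare with either that figure or a corrected one.

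**What to change.** In the Sample Size Calculations section, recompute the hypothesis 2 detectable difference from the expected number of children aged 6 to under 24 months per camp. State where that number comes from, or the age assumption behind it, and show a range. Confirm that the SD of 2 applies to that age band.

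Alternatively, if all under-fives are intended, change the age band in the Outcome measures section to match the calculation.

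In either case, limit the closing sentence to the outcomes and effect sizes that were calculated.

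The cost is Protocol wording and a short recalculation. All households in the 20 camps are already invited, so enrolment and allocation do not change. If the outcome definition is kept, the price is a less favourable stated figure. If the age band is widened instead, the outcome itself changes.
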